**TOXICITY, ADVERSE REACTIONS ADVERSE EVENTS OR PROBABLE & POSSIBLE SECOND STUDIES ALREADY 'MADE:**

The administration of DHA is generally well tolerated. Supplementation of vitamin D is generally well tolerated when taken at recommended doses. The main adverse effects are in fact linked to an overdose resulting in hypercalcemia and its complications.

**PROCEDURES FOR REPORTING AND REGISTRATION OF ADVERSE EVENTS AND / OR ADVERSE REACTIONS**: Adverse events tab

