**Research objectives**

Efficacy and tolerability of treatment with DHA and vitamin D in children with nonalcoholic steatohepatitis:

- Evaluating the effectiveness of DHA + Vitamin D in improving 'NAFLD Activity Score' (NAS) of the disease

- Evaluation of the tolerability of the administration of DHA and vitamin D

- Evaluating the effectiveness of DHA and vitamin D in improving haematochemical values 'marker' of the evolution of the metabolic syndrome

**Primary endpoint:** the reduction of the score of the disease in the experimental group compared to the control group.

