**CRITERIA FOR THE INTERRUPTION OF TREATMENT:**

Adverse events

All adverse events which occurred during the course of the clinical study will be reported in the case report form that will be completed for each individual patient. An adverse event is defined as any adverse change with respect to the patient's pre-treatment basal conditions regardless of whether the event is or is not considered treatment-related. This includes all relevant laboratory abnormalities and new illnesses that occur or worsen during the treatment period. It is considered treating any medication administered during the study. The intensity of adverse events will be evaluated using a 3-point scale (mild, moderate, severe). It must also be always documented the relationship between the adverse event and the treatment in progress.

| Severity of adverse events | |
| --- | --- |
|  | |
| Mild | You notice a malaise, but do not have any impairment of normal daily activities |
| Moderate | Malaise enough to reduce or affect normal daily activities |
| Severe | Incapacitating with inability to work or perform normal daily activities |
| Life-threatening | It represents an immediate threat to the patient's life |

Any adverse reactions will also be classified according to the "grading" NCI / NIH (see Annex). In case of serious adverse events, the Ethics Committee will be warned.

Laboratory tests on the safety of the treatment:

- The toxicity data be evaluated based on the exams required by the study design.

The treatment will be suspended the following conditions:

- Toxicity of grade III-IV according to the NCI / NIH criteria;

- If the patient expressing the intention to stop treatment

The expected period of the Experiment: 12 months in total including six months for enrollment and 24 weeks in patient enrolled.

SCHEDULED DATE FOR START OF EXPERIMENTS: October 2013

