**METHOD FOR MANAGEMENT, EVALUATION AND PROCESSING AND DISTRIBUTION OF PRELIMINARY AND FINAL DATA:**

At the screening visit (T0), the following controls are provided:

- Complete medical history;

- Complete physical examination;

- Blood count with differential;

- Liver function parameters: AST, ALT, total and fractionated bilirubin, alkaline phosphatase, gamma GT, albumin, total protein and electrophoresis proteinaemia, INR, total cholesterol, triglycerides, blood glucose, alpha-fetoprotein, LDH;

- Renal function parameters: blood urea nitrogen and creatinine;

- Electrolyte balance: Sodium, potassium, calcium and magnesium;

- serum iron and ferritin

- OGTT;

- Vitamin D

- Ultrasound abdomen.

The T1 visit, carried out after 6 months of treatment, will be performed the following investigations:

- Clinical evaluation;

- blood exam completed;

- Liver function parameters: AST, ALT, total and fractionated bilirubin, ALP, gamma GT, albumin, total protein and electrophoresis proteinaemia, INR, total cholesterol, triglycerides, blood glucose, alpha-fetoprotein, LDH;

- Vitamin D values

- 5 ml of blood for serum bank.

At the end of study, performed after 12 months of study, we will be performed the following investigations:

- Clinical evaluation;

- blood exam completed;

- Liver function parameters: AST, ALT, total and fractionated bilirubin, alkaline phosphatase, gamma GT, albumin, total protein and electrophoresis proteinaemia, INR, total cholesterol, triglycerides, blood glucose, alpha-fetoprotein, LDH;

- Vitamin D values

- 5 ml of blood for serum bank

-Liver biopsy.

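### Hypercalcaemia is the named vitamin D harm and tolerability is an objective, yet calcium and renal function are scheduled only at baseline

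*Protocol*

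**What the plan says.** The toxicity section of the protocol makes two statements about vitamin D. The first is reassuring: "Supplementation of vitamin D is generally well tolerated when taken at recommended doses". The second names the harm: "The main adverse effects are in fact linked to an overdose resulting in hypercalcemia and its complications". Under Research objectives, one of three items is "Evaluation of the tolerability of the administration of DHA and vitamin D".

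The visit lists are in the section on management and evaluation of data. The T0 list includes "Electrolyte balance: Sodium, potassium, calcium and magnesium" and "Renal function parameters: blood urea nitrogen and creatinine". The next list opens with "The T1 visit, carried out after 6 months of treatment, will be performed the following investigations" and contains a clinical evaluation, a loosely worded blood-exam item, an itemised liver panel that includes albumin, vitamin D, and 5 ml for the serum bank. The 12-month list is the same with a liver biopsy added. Neither later list has an electrolyte line or a renal line.

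The section on interruption of treatment says how laboratory safety is judged: "The toxicity data be evaluated based on the exams required by the study design". One of its conditions for suspending treatment is "Toxicity of grade III-IV according to the NCI / NIH criteria".

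**The concern.** The protocol identifies a laboratory harm, makes tolerability an objective, and ties the toxicity evaluation to the scheduled tests. It then schedules the relevant tests once, before the first dose. An adverse change from baseline needs two values, and the design asks for only one.

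Two consequences follow. The arms cannot be compared on calcium or renal function at the end of treatment. And if the final report says that no hypercalcaemia occurred, a reader cannot tell a true absence from an absence of measurement. A statistical analysis plan cannot repair this, because it can only analyse values that the visit schedule collects.

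**Working it through.** **Schedule, item by item** (visit lists in the management and evaluation section; baseline serum banking from the section on type of study and experimental design):

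| Item | T0 | T1 (6 months) | 12 months |
| --- | --- | --- | --- |
| Calcium (within electrolytes) | named | not named | not named |
| Blood urea nitrogen | named | not named | not named |
| Creatinine | named | not named | not named |
| Albumin | named | named | named |
| Vitamin D level | named | named | named |
| Serum bank | sample at study entry | 5 ml | 5 ml |

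At T1 the count is 0 of 3 for calcium, urea and creatinine. The 12-month visit also has 0 of 3. I give it no weight for this purpose, because dosing lasts 24 weeks and that visit falls about 52 − 24 = 28 weeks after the last dose.

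**Other routes to a calcium value.** The only other laboratory follow-up described is the monthly control triggered by transaminases at 6 times normal or more. It names liver tests and protein immunoelectrophoresis, not calcium or renal function. No section schedules any of the three analytes after baseline.

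**The loosely worded blood item at T1.** It stands where the T0 list has the blood count with differential, and the liver chemistry is itemised separately beside it. At T0 calcium and creatinine have their own lines; at T1 those lines are gone. A full blood count is therefore the likelier meaning, although a broader panel cannot be excluded.

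**What a T1 calcium would provide.** The sample size section gives 30 evaluable and 33 enrolled per arm. Its stated 83% power reproduces: exact enumeration of the two-sided Fisher test at 45% vs 10% with 30 per arm gives 0.830. The present point does not depend on that figure; it only takes the arm sizes from there.

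With 0 raised values among n treated children, the exact one-sided 95% upper bound on the rate is 1 − 0.05^(1/n):

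- n = 30: 1 − 0.05^(1/30) = 0.0950, or 9.5%
- n = 33: 1 − 0.05^(1/33) = 0.0868, or 8.7%

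The chance of seeing at least one case is 1 − (1 − p)^n. The true rate p is assumed, since the protocol gives none:

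| Assumed p | n = 30 | n = 33 |
| --- | --- | --- |
| 1% | 26% | 28% |
| 5% | 79% | 82% |
| 10% | 96% | 97% |

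With no calcium value scheduled after baseline, there is no bound to state, and an asymptomatic case has no planned route to detection.

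**The case against.** The strongest reply is that the harm is conditional on overdose and this trial does not obviously overdose anyone. The product is fixed, treatment lasts at most 24 weeks, and entry requires reduced vitamin D and normal renal function. Vitamin D itself is measured at T1, so the step before hypercalcaemia is watched in both arms. This stands as a reason to expect a low rate. It does not supply the missing result: a vitamin D level shows exposure, not calcium. The daily dose is also not settled by the text. The product data give 800 IU without saying whether that is per pearl or per day, and the introduction gives two capsules a day, so the daily amount is 800 or 1600 IU depending on the reading. No adjustment for age or weight is stated across ages 4 to 16.

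Four further points deserve credit:

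- **Renal tests.** The toxicity section mentions complications of hypercalcaemia without naming the kidney. Calcium is the core omission; urea and creatinine are a reasonable extension.
- **Stopping rule.** A T1 value arrives when dosing is over, so adding it there cannot serve the grade III-IV rule. That is correct, and the gain is limited to end-of-treatment tolerability data.
- **Banked serum.** Samples from entry and each semester could be assayed later. This softens the gap, but no calcium assay on them is planned.
- **Clinical cover.** Adverse event reporting and the clinical evaluation at T1 would pick up symptomatic cases. Only asymptomatic change is uncovered.

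If the blood item at T1 was meant to include these analytes, the defect is one of wording, and naming them resolves it.

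**Conclusion.** The concern holds. Calcium, urea and creatinine are named only before treatment, so asymptomatic hypercalcaemia or renal change by the end of the course would not be systematically detected, and the tolerability objective cannot be addressed for the vitamin D harm that the protocol itself names. The conclusion rests on reading the T1 blood item as a blood count. On the broader reading the tests might be done, but the text could not be relied on to secure them.

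The importance is modest. The primary efficacy analysis is unaffected, the harm is tied to overdose, and even complete T1 data with no events would exclude only rates above roughly 9%. The point should still be fixed, because the correction is cheap and the participants are children.

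**What to change.** Add serum calcium, blood urea nitrogen and creatinine to the T1 list by name. Read calcium with the albumin already measured at that visit, and report the shift from baseline by arm. If the existing blood item was intended to cover these tests, say so there explicitly. Repeating them at 12 months is optional, since that visit is off treatment.

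The cost is three routine assays per child at one visit: 3 × 60 = 180 to 3 × 66 = 198 assays, on blood already drawn, with a short change to the protocol text and no added visit or venepuncture. This does not provide early detection during dosing. If the sponsor wants calcium or creatinine to inform the stopping rule, an additional on-treatment blood draw is needed.

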**METHOD FOR MANAGEMENT, EVALUATION AND PROCESSING AND DISTRIBUTION OF PRELIMINARY AND FINAL DATA:**

At the screening visit (T0), the following controls are provided:

- Complete medical history;

- Complete physical examination;

- Blood count with differential;

- Liver function parameters: AST, ALT, total and fractionated bilirubin, alkaline phosphatase, gamma GT, albumin, total protein and electrophoresis proteinaemia, INR, total cholesterol, triglycerides, blood glucose, alpha-fetoprotein, LDH;

- Renal function parameters: blood urea nitrogen and creatinine;

- Electrolyte balance: Sodium, potassium, calcium and magnesium;

- serum iron and ferritin

- OGTT;

- Vitamin D

- Ultrasound abdomen.

The T1 visit, carried out after 6 months of treatment, will be performed the following investigations:

- Clinical evaluation;

- blood exam completed;

- Liver function parameters: AST, ALT, total and fractionated bilirubin, ALP, gamma GT, albumin, total protein and electrophoresis proteinaemia, INR, total cholesterol, triglycerides, blood glucose, alpha-fetoprotein, LDH;

- Vitamin D values

- 5 ml of blood for serum bank.

At the end of study, performed after 12 months of study, we will be performed the following investigations:

- Clinical evaluation;

- blood exam completed;

- Liver function parameters: AST, ALT, total and fractionated bilirubin, alkaline phosphatase, gamma GT, albumin, total protein and electrophoresis proteinaemia, INR, total cholesterol, triglycerides, blood glucose, alpha-fetoprotein, LDH;

- Vitamin D values

- 5 ml of blood for serum bank

-Liver biopsy.

**DATA ANALYSIS AND EVALUATION OF RESULTS:**

Sample Size and Statistical Analysis

Statistical tests: Fisher's exact test

Type I error (Alpha) 0.05

Probability (Pi): 0.10 vs 12:45

sample size (n): 33 per arm

Power = 83.00%

***

Consider that 10% of the placebo group reduces the NAS to values ​​<2 (1.2) and that with 30 patients per group will have an 83% power to declare statistically significant at a 0.05 alpha level an absolute difference 35% of the response (45% experimental group - 10% of the placebo group).

Whereas a 10% drop-out, the number of final patients to be enrolled will be equal to 66.

Randomization

Randomization is achieved by the use of random number tables, the sequence is generated by the computer with allocation in a sealed envelope (epidemiology and statistics service). The key to encode the patient will be taken from the pharmacy, as the doctor in charge will remain blinded to the allocation of the patients in the two arms, one with mixture of DHA and vitamin D, and the placebo.

The analysis will be "intention to treat", understood each patient in the original randomization arm.

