**Inclusion Criteria:**

Biopsy consistent with the diagnosis of NAFLD/NASH

Reduced serum levels of vitamin D aminotransferases (ALT) levels <10 upper limit of normal

hyperechogenicity at liver ultrasound examination suggestive of fatty liver

International normalized ratio (INR) < 1,3 Albumin > 3 g/dl total bilirubin < 2,5 mg/dl

No previous gastrointestinal bleeding

No previous portosystemic encephalopathy

Normal renal function

No hepatitis B, hepatitis C infection

Normal cell blood count

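### The one named analysis, an unadjusted Fisher's exact test on reaching a low NAS, is valid but conservative and makes no use of the entry NAS; Boschloo's test plus a supportive baseline-adjusted score comparison would improve it cheaply

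*Protocol*

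**What the plan says.** Under Research objectives, the protocol gives the primary endpoint as "the reduction of the score of the disease in the experimental group compared to the control group". The first objective there identifies the score as the NAS. No cut-off is given, and the text does not say whether a mean change or a proportion is meant.

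Under DATA ANALYSIS AND EVALUATION OF RESULTS, the only procedure named is "Statistical tests: Fisher's exact test", with "Type I error (Alpha) 0.05". The sample size rests on a responder proportion. It assumes that "10% of the placebo group reduces the NAS to values" printed as <2 (1.2), and sets this against 45% in the treated arm ("45% experimental group - 10% of the placebo group"). Thirty children per arm are said to give 83% power; 33 per arm are enrolled to allow for 10% drop-out. The parameter list prints the rates as "Probability (Pi): 0.10 vs 12:45", evidently 0.10 v 0.45. No covariate is mentioned.

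The Inclusion Criteria require "Biopsy consistent with the diagnosis of NAFLD/NASH" and set no minimum NAS. A further liver biopsy is listed for the end-of-study visit at 12 months. EVALUATION OF THE TREATMENT names a different primary parameter: normal transaminases and less fibrosis.

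**The concern.** A test of who ends at or below a fixed NAS does not use where each child started. If a final score of 2 counts as a response (the printed cut-off leaves this unclear), a fall from 3 to 2 is a success, while a fall from 7 to 3 counts the same as no change. Because eligibility sets no minimum NAS, entry scores may differ widely, and with them each child's distance from the cut-off. Nothing in the protocol's fixed analysis estimates the size of the score reduction, although that is what the Research objectives name.

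Separately, Fisher's exact test is known to be conservative with small arms, so some of the 0.05 may go unused. In a trial of 66 children, each asked for a follow-up liver biopsy, avoidable loss of power matters.

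**Working it through.** **Inputs from the protocol.** Response rates 0.10 and 0.45; alpha 0.05; 30 evaluable and 33 enrolled per arm; 1:1 allocation. Sidedness is not stated.

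**1. The plan's own figure.** With X ~ Bin(n, 0.45) and Y ~ Bin(n, 0.10), power = Σ P(X = x) P(Y = y) over all tables (x, y) with Fisher p ≤ 0.05.

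- Two-sided, n = 30: 83.0%. The stated 83% reproduces, so the test is evidently two-sided.
- Two-sided, n = 33: 86.4%.
- One-sided, n = 30: 89.8%, which does not match.

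**2. True size of Fisher's test.** Put the same response rate π in both arms and take the maximum rejection probability over π: 0.027 at n = 30 and 0.036 at n = 33.

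**3. Boschloo's test.** It uses the Fisher p-value as its statistic, but widens the rejection region as far as the maximum size over π stays at or below 0.05. At n = 30 that means rejecting when the Fisher p-value is at most about 0.069 (maximum size 0.047); at n = 33, about 0.077 (maximum size 0.049).

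| n per arm | Fisher: max size | Fisher: power | Boschloo: power | Gain (points) |
|---|---|---|---|---|
| 30 | 0.027 | 83.0% | 85.6% | 2.6 |
| 33 | 0.036 | 86.4% | 91.1% | 4.7 |

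These figures use only the protocol's inputs. The row for 33 assumes that all 33 children per arm contribute at the planned rates.

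**4. Comparing the score itself.** The protocol gives no NAS standard deviation, no baseline correlation and no shape for the treatment effect. What follows is therefore assumption-based.

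*(a) Every child's score shifts by the same amount.* Assume a roughly normal score with SD 1.5 and a 1-point shift, with 10% of the placebo arm at or below the cut-off. The treated response rate is then Φ(−1.282 + 1/1.5) = Φ(−0.615) = 0.269, and Fisher's power at n = 30 is 27%. For the adjusted score comparison, power = Φ(1 / [1.5 √(1 − ρ²) √(2/30)] − 1.96), where ρ is the correlation of baseline with final score:

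- ρ = 0: Φ(2.58 − 1.96) = 73%
- ρ = 0.5: Φ(2.98 − 1.96) = 85%

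Simulating an integer 0–8 score with ρ = 0.5 gives about 80% for ANCOVA and 28% for Fisher.

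*(b) Some children resolve and the rest do not change systematically.* Assume responders (10% v 45%) fall to 1–2 and non-responders stay at 3 or above with random variation; entry mean 3.5–5, SD 1.3–1.5; n = 30. In simulation, Fisher has 82–85% power and ANCOVA 65–75%.

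The ranking reverses between (a) and (b), and both are compatible with what the protocol says.

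**The case against.** The strongest reply is that the plan has made a legitimate choice. The Research objectives do not say whether reduction means a mean change or a proportion of children. The sample-size text counts children whose NAS is reduced to a low value, which is a workable if coarse version of the stated endpoint. Fisher's test is valid, its power reproduces, and covariates or supportive analyses may sit in a statistical analysis plan that is not shown. All of this stands, and it limits the point to an improvement.

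Four stronger readings are tempting but unsupported:

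- *That the plan does not test its primary endpoint.* It tests a threshold form of it. The textual fault is that the endpoint is described in three different ways.
- *That most of the biopsy information is lost.* This holds only under an assumed uniform shift. If benefit is resolution in a subset, the responder test is the more powerful one.
- *That a chance baseline imbalance could be mistaken for an effect.* Under randomisation the unadjusted test already averages over such imbalance, and its size is at most 0.027 at 30 per arm. Adjustment gains precision; it repairs no false-positive problem.
- *That moving to the score has no downside.* The criteria ask for a consistent biopsy, not a scored one, and the screening list contains no biopsy, so a comparably scored entry NAS is an inference. Missing final biopsies also need a rule in a score analysis.

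What the reply does not remove is that the protocol itself fixes Fisher's test, and that a uniformly at least as powerful test of the same hypothesis at the same level is available.

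**Conclusion.** The point holds as a cheap improvement and does not show an invalid analysis. On the protocol's own inputs, replacing Fisher's test by Boschloo's gains 2.6 percentage points of power at 30 per arm and 4.7 at 33, with type I error still held at 0.05. The fixed analysis makes no use of the entry NAS and gives no estimate of the score reduction that the Research objectives name; a baseline-adjusted comparison would supply one. Whether that comparison would also be more powerful cannot be settled from the protocol: about 80% v 28% in its favour under an assumed uniform 1-point shift with SD 1.5, but about 65–75% v 82–85% against it under assumed resolution in a subset. The documents therefore do not support requiring the responder endpoint to be replaced.

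**What to change.** In the data analysis section:

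1. Keep the responder proportion as the formal test, state that it is two-sided at 0.05, and replace Fisher's exact test with Boschloo's.
2. Add, as the first supportive analysis, end-of-study NAS compared between arms by ANCOVA with the qualifying-biopsy NAS as covariate, reporting the adjusted mean difference with its 95% confidence interval.
3. State one primary endpoint, worded identically under Research objectives, EVALUATION OF THE TREATMENT and the sample-size text, and say whether a final NAS of 2 is a response.

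Making the adjusted score comparison primary remains open to the sponsor, but should be justified by the form of effect expected.

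The cost is one rewritten paragraph and one extra model, with no new patients, visits or biopsies. The entry biopsy must be NAS-scored, the score analysis needs a rule for missing final biopsies, and Boschloo's test takes slightly more computation.

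### The protocol attaches 83% power to both 33 and 30 per arm; it belongs to 30 evaluable per arm and is not the power of the declared intention-to-treat analysis

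*Protocol*

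**What the plan says.** Everything needed stands in the Protocol, section DATA ANALYSIS AND EVALUATION OF RESULTS.

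- **The list:** "Statistical tests: Fisher's exact test", "Type I error (Alpha) 0.05", "Probability (Pi): 0.10 vs 12:45", "sample size (n): 33 per arm", and a power of 83.00%.
- **The paragraph below it:** "with 30 patients per group will have an 83% power to declare statistically significant at a 0.05 alpha level" for "an absolute difference 35% of the response (45% experimental group - 10% of the placebo group". It then allows 10% drop-out and arrives at 66 children to enrol. The POPULATION STUDY section confirms 33 per arm.
- **Under Randomization:** "The analysis will be 'intention to treat', understood each patient in the original randomization arm".

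The protocol does not say how a randomised child without the 12-month liver biopsy is to be counted.

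**The concern.** One power figure is attached to two sample sizes, and with one test, one alpha and one pair of response rates both cannot be right. A reader of the list alone takes 83% as the power of the enrolled trial. A reader of the paragraph takes it as the power after losses.

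There is also a mismatch of basis. A number inflated for drop-out presumes that drop-outs leave the analysis. An intention-to-treat analysis keeps them, and each then needs some outcome. The protocol therefore states power for one analysis and declares another.

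At stake is whether the stated power can be relied on, and whether anyone has seen what it becomes once missing biopsies are handled. The outcome comes from a second liver biopsy in children at 12 months, about six months after treatment ends, so some missing biopsies must be expected.

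**Working it through.** **Inputs.** Fisher's exact test; alpha 0.05; placebo response 0.10; experimental response 0.45 (the list's second rate is garbled, but the paragraph gives 45%); 30 or 33 per arm; drop-out 10%. The protocol does not state sidedness. Two-sided is assumed and tested in step 1.

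**Formula.** Exact power over all 2×2 tables, with a and b the responders on placebo and experimental treatment:

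Power = Σₐ Σ_b Bin(a; n₀, p₀) × Bin(b; n₁, p₁) × 1{Fisher p(a, b) ≤ 0.05}

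**Step 1: reproduce the stated figure.** With p₀ = 0.10 and p₁ = 0.45:

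| Per arm | Fisher, two-sided 0.05 | Fisher, one-sided 0.05 |
|---|---|---|
| 30 | 83.0% | 89.8% |
| 33 | 86.4% | 92.3% |

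The match at 30 per arm, two-sided, shows how the 83% was obtained. The paragraph is right. The list, at 33 per arm, is off by 86.4 − 83.0 = 3.4 points. A continuity-corrected normal approximation gives 84.9% at 33, which is closer, but it is not the named test.

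**Step 2: from 30 to 33.** 30 × 1.10 = 33. Dividing instead gives 30 / 0.90 = 33.3, rounded up to 34. The difference of one child per arm is immaterial. Either way, the 83% is the power with about 30 children per arm left after losses (33 × 0.90 = 29.7).

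**Step 3: all 66 analysed in their arms.** This needs an outcome for the children lost, so each line carries its own assumption. All use 33 per arm and two-sided Fisher.

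| Assumption | Rates | Power |
|---|---|---|
| No losses | 0.10 v 0.45 | 86.4% |
| 10% lost, counted as non-responders | 0.10 × 0.90 = 0.09 v 0.45 × 0.90 = 0.405 | 80.4% |
| Exactly 3 per arm lost, counted as non-responders | 30 at 0.10 v 30 at 0.45, denominator 33 | 81.5% |
| 10% lost, given the placebo rate in both arms | 0.10 v 0.90 × 0.45 + 0.10 × 0.10 = 0.415 | 78.9% |
| 15% lost, counted as non-responders | 0.085 v 0.3825 | 76.9% |
| 20% lost, counted as non-responders | 0.08 v 0.36 | 73.0% |

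**Step 4: sensitivity to the split.** Fisher's test is discrete, so power moves unevenly with arm size. At 0.09 v 0.405, with placebo/experimental numbers:

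| Split | Power |
|---|---|
| 33/33 | 80.4% |
| 32/34 | 84.0% |
| 34/32 | 85.2% |
| 31/35 | 83.6% |

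With 65 children, 33/32 gives 84.7% and 32/33 gives 81.5%.

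**Step 5: an alternative exact test.** At 33 per arm the maximum true size of Fisher's test is 3.6%, against 4.9% for Boschloo's test (Fisher p-value as ordering, size maximised over the common rate on a 0.001 grid).

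| Split and rates | Fisher | Boschloo | Gain (points) |
|---|---|---|---|
| 33/33, 0.09 v 0.405 | 80.4% | 86.3% | 5.9 |
| 32/34, 0.09 v 0.405 | 84.0% | 87.4% | 3.4 |
| 34/32, 0.09 v 0.405 | 85.2% | 87.5% | 2.3 |
| 30/30, 0.10 v 0.45 | 83.0% | 85.6% | 2.6 |
| 33/33, 0.10 v 0.45 | 86.4% | 91.1% | 4.7 |

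**The case against.** The strongest reply is that the paragraph explains the list. It gives 30 per group for 83%, then adds drop-outs to reach 66. Read literally, the list understates power, so the slip is conservative and changes neither the sample size nor any decision. This stands as a limit on the size of the point. The listed pair is still wrong.

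A reader might infer that analysing all 66 children gives only about 80%, and that the trial falls short of its stated power. The documents do not support that. At the protocol's own rates with every outcome observed, 66 children give 86.4%. The 80.4% needs a rule that the protocol does not contain. Its intention-to-treat statement fixes the arm in which a child is counted, not the outcome of a child without a biopsy, and such a rule may properly sit in a statistical analysis plan that is not shown. The figure also belongs to an exact 33/33 split. The protocol describes random number tables and mentions no blocking, so a 32/34 split is plausible, and either way round it puts power above 83%.

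A reader might also infer that Fisher's test is a mistake because it does not use the full 5%. It is a valid test, and conservatism is a known property of it. The larger gain from Boschloo's test, about 6 points, is particular to 33/33; at the other splits of 66 shown it is about 2 to 3.5 points.

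One part of the point survives all of this. The allowance for drop-outs and the declared analysis stand in the same section of the protocol and do not describe the same analysis.

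**Conclusion.** The point holds in two parts.

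1. **Wrong stated pair.** With the named test taken two-sided, 83.0% is the power for 30 evaluable children per arm. The listed 33 per arm gives 86.4% if all outcomes are observed. This rests only on the protocol's inputs and on two-sidedness, which reproduces the stated figure where one-sided testing at 0.05 does not.
2. **Power and analysis on different bases.** The 83% is for an analysis without the drop-outs, while the declared analysis keeps them. The power of the declared analysis cannot be fixed until missing biopsies have a rule. If they count as non-responders, it is about 80% at exactly 33 per arm and 10% drop-out, and about 84 to 85% if the 66 children split 32/34 either way. Across the three rules tried at 33 per arm and about 10% loss, it runs from 78.9% to 81.5%, which is 1.5 to 4.1 points under 83%.

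The effect is modest. The 83% for 30 per group is correct, and nothing here shows that 66 children are too few or that the choice of test is an error.

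**What to change.** **Restate the list** so that it agrees with the paragraph: 30 evaluable per arm, two-sided Fisher's exact test at 0.05, 10% v 45%, power 83%; 33 randomised per arm, power 86% if all have outcomes.

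**Link power to the declared analysis.** Say, here or in the statistical analysis plan, how randomised children without the end-of-study biopsy are counted, and give the power under that rule. If they are counted as non-responders, add that power is about 80% at exactly 33 per arm and 10% drop-out, and about 84 to 85% if the 66 split 32/34 either way. An analysis of children with a biopsy can be shown as sensitivity.

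**Cost.** Wording only. No extra child and no extra biopsy is needed; the price is that one conditional power figure looks slightly less favourable.

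**Optional.** Boschloo's exact test at two-sided 0.05 would raise power on the same children by about 2 to 6 points, depending on the split. This is more than a wording change, because it replaces the named test and would have to be fixed before unblinding. Its downside is that readers know it less well. Keeping Fisher's test is acceptable.
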